### 2.5. Follow-Up Assessments

Three months after the beginning of the multidomain intervention (T1), a stool sample will be collected for the analysis of the gut microbiota; this is the only assessment planned at T1. At the end of the intervention (6 months, T2) and three months later (9 months, T3), the assessments will be repeated. Furthermore, anthropometric data and blood and stool samples will be collected, together with assessments of physical and cognitive performance, at both T2 and T3. While the 6-month time point will allow us to evaluate the immediate effects of the intervention, the 9-month follow-up is intended to assess the durability of any observed effects, to evaluate whether possible improvements are maintained, attenuated or lost once the intervention is discontinued.

### 2.6. Retention

In order to promote continued participation in the study, a set of strategies will be implemented, as follows: participants will receive regular reminders to attend training sessions (printed notes, announcements by the staff); study staff (nurses, LTCFs coordinators) will encourage participants to follow the suggested activities and to use the smartwatch provided; and, in addition to participants, family members and caregivers will also be informed about the project and the activities. Furthermore, sessions will be adapted, when necessary, and their schedules will be managed flexibly to minimize burden or fatigue. Participants will receive continuous positive reinforcement (verbal encouragement and group support) to help maintain motivation and adherence over time.

With regard to follow-up visits, at the end of each visit, the date of the next visit will be set and instructions given; reminders, such as printed notes, will be delivered to participants’ rooms or handed to them during meals by staff members. Short in-person meetings or group announcements will be organized by staff members to reinforce upcoming sessions or follow-up assessments. Indirect reminders will also be sent to family members, when appropriate, via phone calls or emails from the facilities’ contact person.

### 2.7. Analytical Approach

#### 2.7.1. Outcomes

The feasibility of the multidomain intervention will be assessed by considering the acceptability and the participants’ adherence to the interventions. In particular, feasibility outcomes will include the following:Recruitment and retention rates over the study period;Adherence metrics (attendance at training sessions, completion of cognitive modules, dietary compliance);Technological acceptability, assessed via user feedback and actual usage data (wearable sensors, digital apps);Completeness and quality of data collected across domains;Operational challenges, including staffing, logistics, and data management within LTCFs.

The primary health outcome of this short-term pilot study is the evaluation of changes in gut microbiota composition and the differences between the two groups (multidomain intervention and control groups) at the 3-month follow-up point (T1). The gut microbiota has emerged as a central player in the gut–brain–muscle axis, and growing evidence suggests it may influence metabolism, inflammation, muscle function, and neurocognitive processes, making it a valuable biomarker in multidomain interventions for older adults [54].

Secondary outcomes were selected to reflect the domains of cognitive and functional well-being referenced in the study title and central to the I-COUNT intervention, and will include the assessment of changes in the following:Gut microbiota composition and differences between the two groups at follow-up at 6 and 9 months (T2 and T3);Hemogram, electrolytes, cholesterol, triglycerides, blood glucose, vitamin D, and other parameters and differences between the two groups at 6- and 9-month follow-ups (T2 and T3);Additional biomarkers (including ESR, high-sensitivity CRP, albumin, transferrin, IL-6, BDNF, FT3/FT4, s-RAGE, irisin, IGF1, ghrelin) and differences between the two groups at 6- and 9- months follow-up (T2 and T3);Physical performance (SPPB) and differences between groups at 6- and 9-month follow-ups (T2 and T3);General and domain-specific cognitive functioning (mNTB, ACE-R) and differences between groups at 6- and 9-month follow-ups (T2 and T3);Psychological health (GDS, PSS, DASS), sleep quality (PSQI) and differences between groups at 6- and 9-month follow-ups (T2 and T3);Number of falls and number of hospital admissions and differences between groups at 6- and 9-month follow-ups (T2 and T3);Nutritional, anthropometric status (MNA-SF, BMI, waist circumference), and body composition, and differences between the groups at 6- and 9-month follow-ups (T2 and T3).

#### 2.7.2. Adverse Events

An adverse event, defined as any unintended unwanted outcome, including abnormal laboratory results, symptoms or illnesses, falls, and hospital admissions that occur during the intervention, whether or not related to the intervention, will be reported.

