### 2.1. Study Design

The pilot study will follow a parallel group cluster randomized controlled trial. Randomization will be carried out at the cluster level to minimize the risk of contamination, and clusters will be defined as distinct units within LTCF residencies (i.e., separate floors or buildings, not sharing common areas or group activities, with minimal social interactions between clusters). A 6-month multicomponent intervention will be delivered and compared with usual care. Participants assigned to the multicomponent intervention will receive a 6-month program including Mediterranean diet and functional foods, physical exercise, and cognitive stimulation (see Multidomain intervention section). Participants in the intervention group will also be offered vaccinations according to the national vaccination calendar. The study protocol will include baseline evaluations (T0), a 6-month multidomain intervention, and follow-up assessments at 3 months (T1), 6 months (T2), and 9 months (T3). Participants in the control group will continue the standard care provided in their respective LTCFs, including their usual physical and cognitive stimulation activities, as well as their usual diet. Participants assigned to the control group will receive general information on healthy lifestyle and health, including risk factors. Figure 1 shows the flow diagram of the I-COUNT study protocol.

This protocol was designed in accordance with the CONSORT guidelines for feasibility and pilot studies. See the online Supplementary Materials for the CONSORT checklist figure. Participants or the public were not involved in the design of the study protocol.

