Health problems and symptoms will be evaluated by the physiotherapist or the exercise science expert before starting each session. If a participant reports a significant change in health before or during the exercise, the geriatrician will be consulted. Vital signs (heart rate, blood pressure, and oxygen saturation) will be recorded at the beginning and the end of each session. Physical exercise training sessions will be stopped in the presence of (a) resting systolic blood pressure >200 mmHg or diastolic blood pressure >100 mmHg; (b) resting heart rate >120 beats/min or <40 beats/min; (c) increased heart rate 90% of maximum age during exercise; (d) oxygen saturation <90% in ambient air; (e) unusual or severe dyspnea; (f) oppressive pain or discomfort in the chest, pain in the left arm, indigestion or discomfort in the stomach; (g) palpitations; (h) severe dizziness, fainting or fainting sensation; (i) decrease in diastolic blood pressure by 20 mmHg during exercise; (j) increase in systolic blood pressure to 250 mmHg or diastolic blood pressure to 115 mmHg during exercise; or (k) decrease in oxygen saturation <88% in ambient air during exercise. The clinical conditions of the participants and the levels of intensity and duration of the exercise will be re-evaluated.

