Physical and cognitive interventions will be administered in a smart environment, with technological solutions including mobile and wearable devices, ensuring high acceptability by the users. In particular, smartwatches and tablets with SIM cards and pre-loaded specific applications will be used for physical and cognitive training and for monitoring specific conditions (risk of falls). Health professionals responsible for the different interventions will explain to study participants and to their family members the use of the devices (basic functions, such as turning the device on and off, and opening specific applications).

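### The adverse-event window in section 2.7.2 closes with the 6-month intervention, does not match the falls and admissions outcome that runs to month 9, and is unclear for controls

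*Protocol article*

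**What the plan says.** Section 2.7.2 defines an adverse event as any unintended, unwanted outcome. It names abnormal laboratory results, symptoms or illnesses, falls and hospital admissions, and it limits them in time: "falls, and hospital admissions that occur during the intervention, whether or not related to the intervention, will be reported". It does not name an arm.

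Section 2.1 gives the durations. For the intervention: "A 6-month multicomponent intervention will be delivered and compared with usual care". For follow-up: "follow-up assessments at 3 months (T1), 6 months (T2), and 9 months (T3").

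Two other sections collect the same kinds of event or measurement after month 6. Section 2.7.1 lists among the secondary outcomes "Number of falls and number of hospital admissions and differences between groups at 6- and 9-month follow-ups (T2 and T3"). Section 2.5 says that "anthropometric data and blood and stool samples will be collected, together with assessments of physical and cognitive performance, at both T2 and T3".

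Structured health checks appear only where the intervention is described. In section 2.4.2: "Health problems and symptoms will be evaluated by the physiotherapist or the exercise science expert before starting each session", and "Vital signs (heart rate, blood pressure, and oxygen saturation) will be recorded at the beginning and the end of each session". In section 2.4.3, smartwatches and tablets serve the training and are also used "for monitoring specific conditions (risk of falls").

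**The concern.** A harms rule should cover the period over which participants are followed, and it should mean the same thing in both arms. This one is tied to an intervention that only one arm receives and that ends three months before follow-up does. Section 2.5 gives the month-9 visit the purpose of showing what happens once the programme stops, yet new symptoms or illnesses in those months have no stated route into the adverse-event report.

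A second issue concerns comparability. Intervention residents meet study staff who ask about health problems several times a week, and no comparable contact is described for controls. If what is learned at those meetings enters the counts of falls or other events, the intervention arm could show more events simply because more are noticed. In a pilot meant to inform a larger trial, that could make the programme look less safe than it is or hide a benefit on falls.

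**Working it through.** The plan gives no figure for adverse events. Its one design figure, a detectable effect of 0.52 with 60 per group (section 2.2.1), reproduces: an exact two-sided t-test at 80% power gives 0.516. Nothing below depends on it.

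**Step 1: length of the window.** The intervention lasts 6 months and follow-up 9 months (section 2.1). Outside the window: 9 − 6 = 3 months, and 3/9 = 33% of planned follow-up.

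**Step 2: each event type named in section 2.7.2, in months 6 to 9.**

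| Event type | Adverse event under 2.7.2? | Collected elsewhere? |
|---|---|---|
| Falls | No | Yes, outcome at T3 (2.7.1) |
| Hospital admissions | No | Yes, outcome at T3 (2.7.1) |
| Abnormal laboratory results | No | Bloods drawn at T3 (2.5), as outcomes |
| Symptoms, illnesses | No | No event collection stated |

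A fall in month 8 is therefore an outcome but not an adverse event. An abnormal T3 result is recorded but falls outside the article's own reporting rule. A new illness in month 8 is covered only if it leads to an admission or shows up in a scheduled assessment.

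**Step 3: the control arm.** Controls continue usual care (section 2.1). The time limit in section 2.7.2 can mean the same 6 calendar months for everyone, or only the period of those who receive the programme. The text does not settle which.

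**Step 4: structured contacts up to month 6.**
- Cognitive sessions: 48 in total at 2 per week (section 2.4.3), so 48/2 = 24 weeks.
- Exercise sessions: 3 per week (section 2.4.2), so 3 × 24 = 72 if exercise runs over the same 24 weeks, or 3 × 26 = 78 over 26 weeks. Each has a symptom check and vital signs.
- Controls after baseline: T1, where stool is the only assessment (section 2.5), then T2. No symptom checks are described between visits.

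**Step 5: what unequal capture could do (illustration only).** With equal true rates, the apparent rate ratio is capture in the intervention arm divided by capture in controls. The article gives neither, so both are assumptions. With 95% in the intervention arm:
- controls 95%: 0.95/0.95 = 1.00
- controls 90%: 0.95/0.90 = 1.06
- controls 70%: 0.95/0.70 = 1.36
- controls 50%: 0.95/0.50 = 1.90

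The range starts at no distortion, and the article does not show where the trial would fall.

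**The case against.** Two stronger readings are tempting, and the article supports neither.

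The first is that events after month 6 are dropped. They are not: section 2.7.1 counts falls and admissions in both groups to T3, and section 2.5 draws blood at T3. Three of the four kinds of event are still collected. What they lose is reporting as adverse events; only symptoms and illnesses have no stated collection as events.

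The second is that falls and other events are ascertained unequally, so that the comparison is biased. No section makes the pre-session check a source of event counts. In section 2.4.2 it is a safety screen for exercise. The devices in section 2.4.3 are said to monitor the risk of falls, not to count falls. Falls and admissions are outcomes for both groups, outcome evaluators are blinded (section 2.2.2), and an admission is hard to miss in either arm. No between-group comparison of adverse events as a whole is stated. Blinding does not fully answer the worry, since it governs how an event is judged and not whether it reaches the record, but the point remains a risk.

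It is also fair to say that a journal article condenses, and that collection procedures may stand in the full protocol. That excuses missing detail about sources. It does not excuse the time limit, which the article states and which does not fit its own outcome list.

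**Conclusion.** The point holds as a badly fixed reporting window. Followed as written, section 2.7.2 leaves 3 of 9 follow-up months (33%) outside adverse-event reporting, gives falls and admissions two different windows, and leaves the control window open to two readings. This rests on the stated text and durations alone.

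Detection bias is a conditional risk. About 72 structured checks per intervention resident, against none described for controls, would matter only if those checks feed the counts being compared. They bear most plausibly on symptoms and minor events. No size can be attached without assumed capture rates. The study's sample size is unaffected, and its feasibility aims are not undermined. It is an inexpensive improvement worth making.

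**What to change.** In section 2.7.2:
1. Set the adverse-event reporting period as T0 to T3 for both groups, so that it agrees with the falls and admissions outcome in section 2.7.1.
2. State that between-group comparisons of falls and admissions use a source and a collection schedule that are the same in both arms. The article does not describe what records the facilities keep, so the sponsor has to name the source.
3. Report events found only through session checks or devices separately, as safety data for the intervention arm.

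The cost is a change of wording and slightly more event collection in months 6 to 9. Under item 3, events seen only at sessions leave the comparison. Some of these may be exercise-related harms, so the separate report must appear alongside it. No extra participants are needed.

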#### 2.7.3. Statistical Analyses

Descriptive statistics will be calculated in relation to feasibility measures (recruitment and retention rates over the study period, adherence metrics, technological acceptability, completeness of data collected and operational challenges).

Continuous variables will be compared between groups through mixed models, with random effects at the cluster level and treatment group as fixed effects. The potential health impact of multidomain interventions will be estimated considering changes over time for continuous variables analyzed through mixed models for repeated measures, with group and time, and group x time interaction as fixed effects, and cluster and patients as random effects.

The continuous variables considered in comparison between groups for fecal microbiota analyses will include measures of species richness (α-diversity), the relative abundance of specific bacterial taxa, and the representation of genes involved in key bacterial metabolic pathways. The effects of the intervention on the overall fecal microbiome composition will also be assessed comparing intervention and control groups on different time points with Bray–Curtis dissimilarity on principal coordinate analysis.

Data available for participants with complete data will be considered, but also an intention-to-treat (ITT) approach with imputation for missing data will be applied.

Results with a *p*-value < 0.05 will be considered statistically significant. Analyses will be performed using SAS software version 9.4 (SAS Institute, Cary, NC, USA).

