#### 2.2.1. Sample Size

The endpoint related to sample size refers to changes in gut microbiota composition between the two groups (multidomain intervention; control) assessed at 3-month follow-up compared to baseline. As suggested by Sim and Lewis to maximize precision and efficacy for pilot studies [29], a sample size of 30 individuals in the intervention group and 30 individuals in the control group is planned for each participating LTCF. This resulted in a total of 60 participants per group (120 in total). This allows for the detection of an effect size of 0.52 with 80% power and alpha = 0.05, considering a simplified approach assuming a two-sample *t*-test with equal variance (PASS 2024, version 24.0.1).

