#### 2.2.2. Randomization and Blinding

Two LTCFs will participate in the I-COUNT study, and within each LTCF, two units (floors or flats) will be randomly assigned to either the intervention or control group using the SAS Plan procedure. Participants will not be informed of their group allocation until the completion of the baseline assessment. Outcome evaluators will be blinded to participants’ group assignments, and participants will be instructed not to disclose this information to the assessors. The geriatricians and neuropsychologists responsible for developing the training activities will be different from the outcome assessors. If maintaining blinding for the outcome assessors is not feasible, additional assessors will be recruited to ensure impartiality.

Data will be processed in accordance with the European Regulation on the use of personal data (679/2016) and Legislative Decree no. 196 ss.ii. 30 June 2003, as amended by Legislative Decree no. 101 of 10 August 2018, as well as Deliberation of the Privacy Guarantor no. 52 of 24 July 2008 and subsequent updates.

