The domains addressed in the I-COUNT pilot protocol are crucial for preserving current abilities or delaying the onset of decline in older adults. Moreover, interventions targeting one domain often have positive effects on different domains as well. For example, the reduction in frailty score and improvements in cognitive status are significantly mediated by the composition and functionality of the gut microbiota in individuals following the Mediterranean diet [54]. The beneficial effects of physical exercise on cognitive status are also well documented [58,59]. Finally, vaccination, together with other interventions (e.g., diet, physical training) can contribute to healthy aging, also preserving the independence of older adults [60]. In our opinion, multidomain interventions represent the best option to preserve the health of older adults and protect them from frailty. We expect that positive changes might be observed in each domain during the intervention, as well as improvement in perceived quality of life and psychological status.

All the measures collected before the training and during the follow-ups (including biomarkers, physical performance, neuropsychological and psychological data) will enable us to assess the feasibility of the multidomain intervention protocol, analyze its effectiveness in detail, and to create a biobank for future studies on risk profiles related to the development of cognitive and functional disability. As a pilot and feasibility study, I-COUNT is not designed to test efficacy or effectiveness in a definitive sense but to explore whether the intervention can be successfully delivered in LTCF settings, and to identify operational, technological, and procedural aspects that may require refinement. These outcomes will provide critical information to refine intervention components, improve training procedures, and optimize data collection protocols. Importantly, data from this pilot will be used to calculate effect sizes and variability estimates, which are essential for accurate sample size calculation in a future multicenter randomized controlled trial. Moreover, qualitative and process evaluations will help us better understand barriers and facilitators to implementation in real-world aged care settings.

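### With only four randomised units, the p < 0.05 rule for health outcomes is either too liberal or nearly powerless, and the repeated-measures model leaves out unit-level variation in change

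*Protocol article*

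**What the plan says.** - Section 2.1 (Study Design): "Randomization will be carried out at the cluster level to minimize the risk of contamination".
- Section 2.2.2 (Randomization and Blinding): "within each LTCF, two units (floors or flats) will be randomly assigned to either the intervention or control group".
- Section 2.2.1 (Sample Size): "a sample size of 30 individuals in the intervention group and 30 individuals in the control group is planned for each participating LTCF". Together with Section 2.2.2 this means one intervention unit and one control unit of 30 in each of two facilities. The trial is sized by an individual-level two-sample t-test, openly described as simplified, for "detection of an effect size of 0.52 with 80% power and alpha = 0.05".
- Section 2.7.3 (Statistical Analyses) names two models. In the first, "Continuous variables will be compared between groups through mixed models, with random effects at the cluster level" and treatment group is fixed. In the second, for change over time, group, time and their interaction are fixed, and cluster and patient are random. Neither has a facility term. The section then gives one rule for all results: "value < 0.05 will be considered statistically significant".
- Section 3 (Discussion): "I-COUNT is not designed to test efficacy or effectiveness in a definitive sense". The limitations paragraph there does not mention the number of clusters.

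**The concern.** Treatment varies only between units, and there are four of them. The between-unit variance that should set the standard error of the arm contrast therefore rests on 2 degrees of freedom (4 units less 2 arms), or 1 if facility is also fitted. Within each facility, treatment and unit are fully confounded. A random cluster effect fitted to so few units is often estimated as zero, and the analysis then treats the residents as independent.

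The significance rule carries no exploratory label and covers the primary microbiota outcome at 3 months and the long list of secondary outcomes. What happens on one floor only, such as a change in menu or staffing or an outbreak, could be reported as a significant effect of the intervention and carried into the planning of the larger trial.

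**Working it through.** **Inputs.** From the protocol: 4 units, 2 per arm, 30 residents each, 60 per arm, d = 0.52, 80% power, alpha 0.05 (taken as two-sided). Assumed, because the article gives no ICC: ICC 0 to 0.10, normal data, equal units, no dropout.

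**1. The plan's own figure.** A two-sample t-test with 60 per arm and 118 df has 80.6% power at d = 0.52, and an 80%-power detectable effect of 0.516. The stated 0.52 is reproduced, with all 120 residents taken as independent.

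**2. Between-group mixed model.** The true variance of the arm difference, in SD units, is (2/60) × (1 + 29 × ICC). REML was simulated from the between-unit mean square (2 df) and the within-unit mean square (116 df), with the cluster variance set to zero when the former does not exceed the latter (200,000 null trials).

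| Assumed ICC | 0.01 | 0.02 | 0.05 | 0.10 |
|---|---|---|---|---|
| Design effect 1 + 29 × ICC | 1.29 | 1.58 | 2.45 | 3.90 |
| Cluster variance estimated as zero | 53% | 46% | 32% | 21% |
| Type I error, z reference | 6.0% | 7.8% | 11.6% | 14.8% |
| Type I error, residual df (116) | 5.7% | 7.6% | 11.3% | 14.5% |
| Type I error, df switching between 2 and 118 (approximates Satterthwaite or Kenward-Roger) | 4.5% | 5.7% | 7.1% | 7.3% |
| Type I error, variance bounded at zero, 2 df | 0.02% | 0.05% | 0.3% | 1.1% |
| Type I error, unbounded variance (unit means), 2 df | 5.0% | 5.0% | 5.0% | 5.0% |
| Power of that last test at d = 0.52 | 30% | 26% | 19% | 14% |
| Its 80%-power detectable effect (SD) | 1.17 | 1.30 | 1.61 | 2.04 |

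At ICC 0 the calibrated 2-df test has 36% power and a detectable effect of 1.03 SD. The loss comes mainly from the critical value, 4.30 instead of 1.98. With facility fitted (1 df, critical value 12.7), power is 18% at ICC 0 and 9.5% at ICC 0.10, and the z-reference error rises to 6.2% to 18.6% for ICC 0.01 to 0.10.

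**3. Repeated-measures model.** Read as random intercepts for cluster and patient, the cluster intercept is the same at baseline and follow-up and drops out of each change, so out of the group by time contrast. The model variance of that contrast is proportional to 2/60, while the true variance is (2/60) × (1 + 29 × ρ), where ρ is the ICC of change. Type I error is then about 2 × [1 − Φ(1.96 / √(1 + 29ρ))]:

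- ρ = 0: 5.0%.
- ρ = 0.01: 1.96/√1.29 = 1.73, giving 8.4%.
- ρ = 0.05: 1.96/√2.45 = 1.25, giving 21%.
- ρ = 0.10: 1.96/√3.90 = 0.99, giving 32%. Simulation gives 33%, because the estimated residual variance is slightly too small.

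A degrees-of-freedom correction on the cluster intercept does not change this.

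**4. Reliance on the model.** With one unit per arm in each facility there are 2 × 2 = 4 allocations, so the smallest two-sided randomisation p-value is 2/4 = 0.50 (2/6 = 0.33 if unrestricted). Any p < 0.05 therefore rests on the assumed distribution of unit effects.

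**5. Use for the next trial.** With 2 df, chi-square limits are −2 ln(0.975) = 0.0506 and −2 ln(0.025) = 7.378. A 95% interval for the between-unit mean square runs from 2/7.378 = 0.27 to 2/0.0506 = 39 times its estimate.

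**The case against.** *The degrees-of-freedom method belongs in the analysis plan.* That plan is not shown, and the article is not at fault for leaving out the method. The 6% to 15% figures do depend on a choice that it leaves open. This stands, but only in part: no such choice adds clusters. The reference distributions examined give an inflated error rate, a very conservative test, or a calibrated test with little power.

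*A stable difference between floors cancels from the change analysis.* This stands. A reader might infer that any pre-existing floor difference can pass as an intervention effect. That is possible only in the simpler comparison of values between groups. For group by time the error rate stays at 5.0% if unit effects are constant over time. The exposure there is unit-level variation in change, and its size is unknown.

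*No randomisation test is planned.* True. The minimum p of 0.50 shows what the planned p-values depend on, not that they are wrong.

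*The health findings are already called exploratory.* The Abstract and Conclusions say so, feasibility is analysed descriptively, and no stated go/no-go decision depends on p < 0.05. This limits the harm. It does not cancel a written significance rule that covers the primary health outcome, and the Discussion also expects a detailed analysis of effectiveness.

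**Conclusion.** The concern holds in a limited form. With two units per arm, p < 0.05 is not a reliable criterion for the health outcomes. In the between-group model the real error rate is about 6% to 15% under large-sample or residual degrees of freedom, or else 5% with 14% to 36% power at d = 0.52. In the repeated-measures model it can reach about 21% to 33% if the ICC of change is 0.05 to 0.10.

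A reader might go further and say that no valid test exists, or that any significant result is uninterpretable. The documents do not support either. A 2-df test on unit means is valid if unit effects are normal, and nothing in the article rules it out.

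The sizes rest on assumed ICCs, equal units of 30, normal data and no dropout. The repeated-measures figures also rest on reading the random effects as intercepts. They concern continuous outcomes and do not cover the Bray–Curtis comparison.

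**What to change.** In Section 2.7.3, replace the significance rule for all health outcomes, including the microbiota outcome at 3 months. Suggested text: *Group differences in health outcomes are exploratory and will be reported as estimates with 95% intervals, without claims of statistical significance.*

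Then:

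- Base the intervals on cluster-level degrees of freedom (2, or 1 with facility fitted), without truncating the between-unit variance at zero.
- For change outcomes, analyse unit-level mean changes or add a cluster-by-time random effect. Unbounding the cluster intercept alone does not reach this contrast.
- Add a small table of intervals with the standard error fixed at assumed ICCs of 0.01, 0.05 and 0.10. In SD units the half-widths are 1.96 × √((2/60) × (1 + 29 × ICC)) = 0.41, 0.56 and 0.71.
- In the limitations paragraph of the Discussion, state that there are four clusters, that unit and treatment are confounded within each facility, and that the between-unit variance passed to the next trial rests on at most 2 degrees of freedom.

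The cost is wording and one table. The downside is wide intervals. With the standard error at its expected value, the 2-df half-width is 4.30 × 0.207 = 0.89 SD at ICC 0.01 and 4.30 × 0.361 = 1.55 SD at ICC 0.10. With facility fitted, 12.7 × 0.207 = 2.6 SD is close to uninformative, so the choice of 2 or 1 should be made beforehand. No significance claim can be made, which agrees with the stated purpose of the pilot.
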